### Instrumentation and Measurements

The instrumentation and measurement tools will include:

#### Self reported outcome measures

##### Numerical Rating Scale (NRS)

This 11-point scale (0-10 where 0 is no pain at all, and 10 is the worst pain imaginable) is ommonly used in the assessment of pain [33], and is a core outcome measure in clinical rials of chronic pain patients [34,35].

##### Tampa Scale for Kinesiophobia (TSK-II)

This scale measures the degree of fear of movement and/or re-injury, and is commonly used in acute and chronic pain populations [36]. It consists of an 11-item self-report questionnaire scored on a four-point Likert scale. The TSK-II consists of two subscales; a somatic focus subscale (items 3, 4, 6, 7, and 10) that reflect the beliefs that there is something seriously wrong with the body, and an activity avoidance subscale (items 1, 2, 5, 8, 9, and 11) that reflects the beliefs that avoiding exercise or physical activities might prevent an increase of pain. A reduction of at least four points on both measures maximises the likelihood of correctly identifying an important reduction in fear of movement. The reliability of the TSK-11 has been established [36].

##### SF-36 Health Survey

This tool will be used to measure health related quality of life (HRQL) and physical functioning [37]. It consists of 36 items that measures 8 multi-item variables including physical functioning, social functioning, role limitations due to physical problem, mental health, energy and vitality, pain and general perception of health, there is also one extra un-scaled item to assess a patient's perceived change in health in the last year. The SF36 is a validated and reliable tool with a high internal reliability value across all items >0.7 except those in the social dimension which were found to be >0.5 [38,39]

##### The Hospital Anxiety and Depression Scale (HADS)

This questionnaire will be used to assess a patient's level of anxiety and depression. It is divided into two subscales; an anxiety subscale (HAD-A) and a depression subscale (HADS-D). Both subscales contain 7 intermingled items. Scores of 11 or more on either subscale are considered to represent a significant case of psychological morbidity, scores of 8-10 represents borderline psychological morbidity and scores of 0-7 represent normal levels of anxiety and/or depression [40]. The HADS has high mean levels of internal consistency HAD-A 0.83 and HAD-D 0.82 (Cronbach's alpha), and a sensitivity and specificity of 0.8 for both HAD (A) and HAD (D)[41].

##### Pittsburgh Sleep Diary (PghSD)

This tool will be used as an adjunct for the Actiwatch AW7 to give a written recording for the objective Actiwatch data. It will be filled in every day for the 7 days that the patient wears the Actiwatch. The instrument comprises two separate sections; a bedtime component that will be filled in just before bed, and a wake time component that will be filled in first thing in the morning. The bedtime component documents events preceding that nights' sleep that may have an impact on sleep quality or quantity; the number of caffeinated drinks consumed, or the number of daytime naps. The wake time component documents events that occur during the night that may impact on that night's sleep such as the number of wake bouts during the night, and patient satisfaction of sleep quality. The PghSD measures of both sleep timing and sleep quality has been shown to have correlations between 0.56 and 0.81 (n = 39, P < 0.001) [42].

### Sleep

#### Sleep

Objective sleep quality will be measured using the Actiwatch AW7 (Cambridge Neurotechnology). Whist not as accurate as the gold standard of sleep assessment, actigraphy has been shown to correlate reasonably well with polysomnography; with intraclass correlation co-efficient of 0.76 for total sleep time, 0.61 for sleep efficiency, and 0.58 for both wake after sleep onset and sleep fragmentation index measurements [43]. This compact and lightweight electronic device similar in size to a wrist-watch is worn on the non-dominant hand, and measures and records physical movement. It automatically collects and scores data for seven sleep quality parameters: wake after sleep onset percentage, sleep onset latency, actual sleep percentage, mean night-time activity, fragmentation index, number of wake bouts, and sleep efficiency. This movement data is then down loaded and analysed using Actiwatch 7 software. Activity is measured in counts; the number of counts is proportional to the intensity of the movement. The peak intensity of the movement in each second is summed into a user selectable epoch (range two seconds and 15 minutes). Data collected is more accurate with a shorter epoch length [44]. The current study proposes to record data for 7 days using a 30 second epoch length, which has been shown to be adequate for the assessment of sleep disturbance [44].

When a patient is ready to sleep they will press the button on the actiwatch to signal this intention of sleep start. When the patient wakes they will press the button a second time to indicate that sleep has finished, this defines the sleep period for analysis. If a patient forgets to press the button, the Pittsburgh sleep diary will be used to determine the sleep start and/or finish. The actiwatch 7 sleep software can then determine the objective sleep quality outcome measures: wake after sleep onset percentage, sleep onset latency, actual sleep percentage, mean night-time activity, fragmentation index, number of wake bouts, and sleep efficiency.

#### Function

The Simmond's functional assessment tool [45] is a validated battery of physical performance measures designed to assess function in patients with chronic LBP. For the purpose of the current study two of these physical performance measures will be included. The sit-to-stand test (STS) times patients as they get up and down out of a chair five times, repeated twice, and the mean time is recorded. The 360° rollover tests times the patient rolling 360 degrees. The Simmond's battery of tests has been found to have good validity and reliability of between 0.69 and 0.99, with a construct validity of P < 0.0001 [46].

### Data management

All participant data will be coded to ensure anonymity, and stored in a password protected computer, and questionnaires locked in a filing cabinet at the School of Public Health, Physiotherapy and Population Science, University College Dublin, Ireland.

### Sample size/Power calculation

While formal power based calculations are not be necessary for a pilot trial, sample estimates to guide recruitment to this study were based on existing data, using objective sleep disturbance as the primary outcome measure. Actigraphy data from patients with chronic LBP [47] indicated that sleep efficiency percentage (mean = 77.8, Sd 7.8) was the variable which differed most significantly from controls. On this basis, a minimum of 90 subjects will be required to detect a moderate treatment effect (ES 0.6). For the purposes of establishing feasibility, and providing data to inform the design of a future main trial based on our CBT-PMP population, we however aim to recruit 24 patients for each arm of the pilot study.

### Data Analysis

All data will be cleaned and entered into the Statistical Package for the Social Sciences (SPSS, Version 16) for analysis. Baseline and demographic data will be presented using descriptive statistics. Differences from baseline will be calculated for all primary and secondary outcomes. Mean differences, standard deviations and 95% confidence intervals will be calculated for continuous variables. Data will be tested for assumptions of normality and parametric analysis will be performed where this is shown. Non-parametric tests will be performed on all ordinal and non-normally distributed data. All tests will be 2 sided with a critical value of p < 0.05.

Primary Outcome: Between group differences in changes to the primary outcome (objective and self-report sleep measures) from baseline to follow up will be performed with independent t tests or Mann Whitney U tests. An intention to treat analysis will also be performed, where missing data are estimated using regression based multiple imputation methods.

Secondary Outcomes: To establish relationships between the sleep variables and other outcome measures (physical and psychological), multiple linear regression models will be constructed. Univariate regression will first be performed and those variables shown to be associated with the dependent variable will be included in the multivariate model. Backward regression will be used to determine the model of best fit.

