### Study Design

This study is a longitudinal pilot study, with patients recruited from the adult Pain service in the Adelaide and Meath Hospital, Dublin (Figure 1). Potential patients who fulfil the inclusion criteria for participation on the multidisciplinary CBT-PMP will be invited to participate in the study by the principle investigator (PI). The study protocol will be reviewed with potential participants, and all questions answered regarding the study. One week later, following a cooling off period, written consent will be obtained, and participants will complete the Pittsburgh Sleep Quality Index (PSQI). Those patients with a sleep disturbance (PSQI >5) will be assigned to either the intervention group (immediate treatment), or control group (deferred treatment, i.e. the PMP they are listed for is more than six months away) based on where they appear on the waiting list. Group membership will be concealed from the PI. To be eligible to take part in the study, participants must fulfil the following criteria:

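### The non-randomised primary comparison is fixed as an unadjusted test of change, with no baseline- or covariate-adjusted estimate of the group effect planned

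*Protocol article*

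**What the plan says.** Study Design assigns eligible patients to immediate or deferred treatment "based on where they appear on the waiting list"; the Abstract says the same. No randomisation, matching or stratification is described.

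For the primary outcome, Data Analysis sets the quantity to be examined: "Between group differences in changes to the primary outcome (objective and self-report sleep measures) from baseline to follow up". It then fixes the method, saying that this comparison "will be performed with independent t tests or Mann Whitney U tests". The Abstract (Methods/Design) names the same two tests. The choice between them follows a general rule: "Non-parametric tests will be performed on all ordinal and non-normally distributed data".

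Baseline values are used in two ways: "Differences from baseline will be calculated for all primary and secondary outcomes", and "Baseline and demographic data will be presented using descriptive statistics". Regression appears only for a different question: "To establish relationships between the sleep variables and other outcome measures (physical and psychological), multiple linear regression models will be constructed". The second primary analysis deals with missing data, not with group differences: "An intention to treat analysis will also be performed, where missing data are estimated using regression based multiple imputation methods".

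**The concern.** Without randomisation, nothing in the design balances patients near the front of the queue against those more than six months away on pain, mood or baseline sleep. A two-group test on change uses baseline in one fixed way, subtracting it with a coefficient of 1, and uses no other covariate. Two things follow. The estimate is less precise than the planned data allow, which matters at 24 per arm. Any measured prognostic difference between the groups is also left in the comparison, with no analysis to show whether it matters. The rank test, where the rule selects it, allows no adjustment either.

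This is a stated method, repeated in the Abstract, and not a detail left for a later document. Its results are meant to inform a larger trial.

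**Working it through.** **Inputs from the protocol.** SD of sleep efficiency 7.8, effect size 0.6, minimum of 90 subjects, 24 per arm (Sample size/Power calculation); two-sided 0.05 (Data Analysis). The difference in points is 0.6 × 7.8 = 4.68.

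**Assumed.** The baseline-to-follow-up correlation ρ is not given, so 0.3, 0.5, 0.7 and 0.8 are shown. The SD is taken as 7.8 at both visits.

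**The plan's own figure.** A two-sample t test with effect size 0.6, two-sided 0.05 and 80% power needs 44.6, so 45, per arm, or 90 in total. The stated figure reproduces. The protocol does not state the power; 80% is inferred. At 24 per arm, the same calculation gives 53% power.

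**Precision.** In units of SD²:
- variance of a change score: 2(1 − ρ)
- variance after adjustment for baseline: 1 − ρ²
- ratio, adjusted to change: (1 + ρ)/2

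The SE of the group difference is 7.8 × √(variance × 2/24). Power is from the two-sample t test with standardised difference 0.6/√variance and n = 24 per arm.

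| ρ | Variance, change | Variance, adjusted | Ratio | SE in points, change / adjusted | Power, change / adjusted |
|---|---|---|---|---|---|
| 0.3 | 1.40 | 0.91 | 0.65 | 2.66 / 2.15 | 41% / 57% |
| 0.5 | 1.00 | 0.75 | 0.75 | 2.25 / 1.95 | 53% / 65% |
| 0.7 | 0.60 | 0.51 | 0.85 | 1.74 / 1.61 | 75% / 81% |
| 0.8 | 0.40 | 0.36 | 0.90 | 1.42 / 1.35 | 90% / 92% |

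The formulas leave out the lost degree of freedom and the small loss when baseline differs between groups. In a simulation with 24 per arm and no imbalance, the empirical SEs were 2.69 against 2.18, 2.23 against 1.97, and 1.73 against 1.63 points at ρ = 0.3, 0.5 and 0.7, in line with the table.

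**Bias.** Let D be a true baseline difference between the groups, with no treatment effect.
- *Both groups regress to a common mean.* The expected follow-up difference is ρD. The change score gives ρD − D = −(1 − ρ)D; the adjusted model gives 0.
- *Stable different means, parallel trends.* The expected follow-up difference is D. The change score gives 0; the adjusted model gives D − ρD = (1 − ρ)D.

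For an illustrative D of 0.3 SD (2.34 points), (1 − ρ)D is 1.64, 1.17 and 0.70 points at ρ = 0.3, 0.5 and 0.7. Simulation of the first case gave −1.76, −1.05 and −0.69 for the change score, and values within 0.1 of zero for the adjusted model. In the second case the same magnitudes fall on the adjusted model, with the sign reversed.

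**The case against.** The strongest reply concerns bias. A reader might infer that the change score carries the groups' baseline imbalance into the estimate and that adjustment removes it. The documents do not support that. A change score already subtracts baseline, so at most the (1 − ρ) share can remain, and only if the groups regress to a common mean. For groups formed by queue position, stable differences are at least as conceivable, and then the change score is the unbiased method. The protocol does not say which case applies, nor does it show that queue position is related to prognosis: both groups come from one list, one team's suitability decision and the same PSQI threshold. This objection stands, and it is why the two analyses belong side by side.

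Nor can one standard error of baseline imbalance at this size, √(2/24) = 0.29 SD, be presented as bias from the queue. It is the chance imbalance that a randomised trial of 24 per arm would also have, and the larger variance of the change score already includes it. Adding it to the power loss would count it twice.

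A reader might also infer that a switch to Mann-Whitney leaves no effect in sleep-efficiency units. Data Analysis promises mean differences with 95% confidence intervals for continuous variables, without making that depend on the test. What remains is that those differences are unadjusted.

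Finally, this is a pilot that does not claim power for 0.6 at 24 per arm, and the gain is small if ρ is high. That lowers the severity. It does not remove the point, because the plan still tests at p < 0.05 and the Discussion says that the study will determine the programme's impact.

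**Conclusion.** The point holds as one of precision and of unaddressed measured differences; it should be fixed, but it does not invalidate the study. Under equal SDs of 7.8 and assumed correlations of 0.3 to 0.7, the planned analysis forgoes a variance reduction of 35% to 15%, and with it 16 to 6 percentage points of power for a 4.7-point difference. At 0.8 the gain is about 2 points.

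On bias, the conclusion is conditional: the change score and the adjusted model are each unbiased under a different assumption, and the protocol gives no ground for choosing between them. Neither removes unmeasured confounding. The figure of 90 subjects is not in dispute.

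**What to change.** In Data Analysis, and in the matching sentence of the Abstract, specify a linear model of the follow-up value on group and the baseline value of the same outcome, with a small set of baseline covariates named in advance from those already collected (for example NRS pain and HADS depression). Report the adjusted mean difference with a 95% confidence interval, using robust or bootstrap standard errors if residuals are skewed. Report the unadjusted change comparison alongside it and state the assumption behind each, so that a reader can interpret any disagreement. Describe the result as a non-randomised comparison in which unmeasured confounding remains.

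The covariates should be fixed before outcome data are seen. The cost is a few degrees of freedom, which is a reason to keep the list short at 24 per arm, and a little more analysis. No new data are needed.

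### Intention-to-treat with imputation is only an additional analysis; the lead primary comparison names no analysis set, and nothing says which result decides

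*Protocol article*

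**What the plan says.** The Primary Outcome paragraph of Data Analysis in the protocol article describes two analyses of the same outcome.

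- The first covers change in objective and self-reported sleep, "from baseline to follow up will be performed with independent t tests or Mann Whitney U tests". No analysis set is attached to it, and no method for missing values.
- The second follows at once: "An intention to treat analysis will also be performed, where missing data are estimated using regression based multiple imputation methods". Imputation is mentioned only here.

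The general paragraph before it adds three rules: "Non-parametric tests will be performed on all ordinal and non-normally distributed data"; "Mean differences, standard deviations and 95% confidence intervals will be calculated for continuous variables"; and "All tests will be 2 sided with a critical value of p < 0.05".

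The Sample size/Power calculation section gives the scale. It cites "sleep efficiency percentage (mean = 77.8, Sd 7.8" for patients with chronic low back pain and says that "a minimum of 90 subjects will be required to detect a moderate treatment effect (ES 0.6"; for the pilot, "we however aim to recruit 24 patients for each arm of the pilot study". Study Design assigns patients to groups by their place on the waiting list.

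**The concern.** The word for the second analysis is also, so it stands beside the lead comparison and does not define it. A change score exists only where both values were observed. Unless something else is stated, the lead comparison therefore drops every patient without a follow-up value. The protocol tests at 0.05 but does not say which analysis carries the conclusion, so with two answers the choice could be made after seeing them.

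This matters more than usual here for three reasons.

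- The arms have different opportunities for loss. Only the intervention arm has the four-week programme and an extra assessment with a further week of Actiwatch and diary (Assessment, Study Patients). Controls have a baseline and one later assessment (Control Group).
- Assignment is not random, so selective loss adds to whatever imbalance the waiting list leaves.
- With 24 per arm, a few missing patients can move the result, and the pilot is meant to inform a main trial.

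**Working it through.** **1. The plan's own figure.** Inputs: SD 7.8, effect size 0.6 (0.6 x 7.8 = 4.68 points of sleep efficiency), two-sided 0.05. Power is not stated; 80% is assumed.

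- Normal formula: n per arm = 2(1.960 + 0.842)^2 / 0.6^2 = 43.6, so 44 per arm and 88 in total.
- Noncentral t: 44.59, so 45 per arm and 90 in total, with power 0.804.

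The stated 90 reproduces. No numerical error lies behind this point.

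**2. What selective loss would do to the lead comparison.** Let a fraction p of an arm be lost, and let those lost improve by d SD less than those who stay, whose mean change is m.

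- Mean over the whole arm = (1 - p)m + p(m - d) = m - pd.
- The observed-case mean is m, so it overstates the arm's change by pd.
- Shift in the between-group difference = p_I d_I - p_C d_C (I = intervention, C = control).

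The document gives neither p nor d. As an illustration only, take d_I = 0.5 and no bias in controls:

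| Loss in one arm | Shift (SD) | Share of 0.6 | Sleep-efficiency points (x 7.8) |
|---|---|---|---|
| 10% | 0.10 x 0.5 = 0.05 | 8% | 0.39 |
| 20% | 0.20 x 0.5 = 0.10 | 17% | 0.78 |
| 25% | 0.25 x 0.5 = 0.125 | 21% | 0.98 |

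The last column treats 7.8, a cross-sectional SD, as the SD of change. The shift is proportional to d, so doubling d to 1.0 gives 0.10-0.25 SD. If both arms have the same p and d, the shift is zero. If only controls are lost selectively, its sign reverses. Of 24 patients, 10-25% is about 2 to 6 (2.4 to 6.0).

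**3. Loss of power with observed cases only.** At effect size 0.6 the t test has power 0.530 with 24 per arm, 0.456 with 20 and 0.396 with 17. These losses are again assumed.

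**4. Can a rank analysis be pooled over imputations?** This was simulated with 24 per arm, correlation 0.5 between baseline and follow-up, 20% missing depending on baseline (the same mechanism in both arms), 20 regression imputations and 1,500 runs. The Mann-Whitney effect P(X<Y) and its standard error were pooled by Rubin's rules.

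| | Imputed and pooled | Complete-case Mann-Whitney |
|---|---|---|
| Rejection with no effect | 5.1% | 4.7% |
| Rejection at a 0.6 SD shift | 45.3% | 42.1% |

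Pooling works. Because missingness was alike in the two arms, this run tests pooling only; it says nothing about bias from unequal loss.

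**The case against.** **The article condenses a fuller document.** Analysis sets and missing-data detail are often left to an analysis plan, which is not shown. That disposes of any complaint about missing detail, such as how imputations are combined. It does not dispose of this point, because the article itself describes two analyses of the primary outcome and places intention-to-treat second.

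**The lead comparison is never called complete-case.** True. A reader might infer that the plan declares a completer or per-protocol analysis. It does not: that the lead comparison rests on observed pairs is an inference, though the natural one, since a separate imputed analysis would otherwise be redundant. Nor does the text remove patients who stop attending but are still assessed. Only missing outcomes are certainly affected.

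**The direction and size of bias are not shown.** This stands. A reader might infer that the lead result favours the programme. That requires those lost to improve less, and the loss to fall mainly on the intervention arm. The documents state neither, and controls follow the same assessment procedures, so an unreturned Actiwatch can occur in either arm.

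**Pooling under Mann-Whitney.** A reader might infer that the imputed analysis has no valid pooled result wherever the plan switches to ranks. That is wrong. A bare U or p-value does not enter Rubin's rules, but a rank effect with its standard error does, and the planned mean differences with confidence intervals pool in the usual way.

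**It is a pilot and both analyses will be reported.** This limits the stakes, but significance tests are planned and the estimates are to inform a main trial.

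**Conclusion.** The point holds in a limited form. As written, intention-to-treat with imputation is an addition; the lead comparison has no named analysis set and by implication uses observed change scores; and no rule says which result decides. The exposure is conditional: it arises if loss is selective and differs between arms. On assumed inputs (10-25% loss in one arm, 0.5 SD less improvement, no bias in controls) it is 0.05-0.125 SD against a planning effect of 0.6, and it could be zero, larger or of the opposite sign. The planned sample size is unaffected. This is worth correcting before analysis because the change is cheap, but it does not undermine the study.

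**What to change.** Name one primary analysis in Data Analysis:

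- **Set:** all assigned patients, in their assigned group, whatever their attendance.
- **Missing values:** the multiple imputation already planned, using group, baseline sleep, and baseline mood and pain. Controls have no end-of-programme values, so those may enter only an imputation done separately for the intervention arm.
- **Estimate:** a baseline-adjusted mean difference with its 95% confidence interval, pooled by Rubin's rules.
- **Sensitivity analysis:** the complete-case t test or Mann-Whitney comparison of change, with a statement that the primary analysis decides if they differ.

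The data are already to be collected and recruitment does not change. The cost is more than a change of rank, since the baseline-adjusted model replaces an unadjusted comparison of change as the primary estimate; this adds a little analysis work. The primary result would also rest on a missing-at-random assumption, and imputation corrects selective loss only as far as the observed variables predict it. That is why the complete-case result should stay in the report.

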## Method/Design

### Research Objectives

The primary research objective is to investigate the short-term multidisciplinary CBT-PMP on subjective (measured by PSQI) and objective sleep quality (measured by Actigraphy) in patients with chronic pain by comparison with a control group. The secondary objective will investigate changes in function and mood, and then explore the relationship between objective and subjective sleep quality, and physical and psychological outcome measures.

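### Univariate screening followed by backward regression in a 48-patient pilot will make the secondary sleep models look better supported than they are

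*Protocol article*

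**What the plan says.** The protocol article, Data Analysis, sets out the secondary analysis as multiple linear regression relating the sleep variables to the physical and psychological measures. It describes two selection steps. First, "Univariate regression will first be performed and those variables shown to be associated with the dependent variable will be included in the multivariate model". Then, "Backward regression will be used to determine the model of best fit". The only threshold in the section is general: "All tests will be 2 sided with a critical value of p < 0.05". No separate criterion is given for removal in the backward step, the dependent variable is not named, and treatment group is mentioned neither as included nor as excluded.

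On size, Sample size/Power calculation says the investigators "aim to recruit 24 patients for each arm of the pilot study", so 48 in total.

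On purpose, Research Objectives states two things. "The secondary objective will investigate changes in function and mood", and the study will then explore how sleep relates to the other measures. Data Analysis uses the verb *establish* for that second aim. For the first aim, Data Analysis provides differences from baseline, standard deviations and 95% confidence intervals for all outcomes, but it names a between-group comparison only for the primary outcome.

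**The concern.** Both selection steps use the same data that later supply the p-values. Each candidate gets its own chance of passing the screen by luck, and those that pass do so because their sample association was large. The final table then shows p-values, confidence intervals and R-squared that take no account of the search, so all of them lean in the favourable direction.

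The practical risk is over-interpretation. A pilot meant to inform a larger trial could report that some mood or function score is related to sleep, with a respectable R-squared, when the selection procedure alone would produce such a result quite often.

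Two smaller matters belong with this. If the regression pools both groups on change or follow-up scores and omits group, a programme that moves both variables creates association between them even when they are unrelated within groups. And regression of sleep on the other measures does not tell the reader whether function and mood changed more in the treated group, which is the first half of the secondary objective.

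**Working it through.** **The plan's own figure.** No figure is given for the regressions. The one computed figure, 90 subjects for an effect size of 0.6, reproduces if 80% power is assumed (power is not stated): 2 × (1.96 + 0.84)² / 0.6² ≈ 43.6, so 44 per arm and 88 in total; the exact t-test needs 44.6, so 45 per arm and 90. That figure is not in question here.

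**Candidate count**, from the instrument descriptions: pain NRS 1, TSK subscales 2, SF-36 variables 8, HADS subscales 2, timed function tests 2, total 15. It is 14 if only the TSK total is used and 16 if the un-scaled SF-36 item is added. Sleep variables: seven actigraphy parameters plus PSQI, total 8. So there are about 15 candidates if sleep is the outcome and about 8 if sleep is the predictor.

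**Screening step at 0.05, all candidates unrelated to the outcome.**
- Expected false hits per outcome with 15 candidates: 15 × 0.05 = 0.75.
- Chance of at least one, if independent: 1 − 0.95^15 = 0.537 (0.512 for 14, 0.560 for 16). With 8: 1 − 0.95^8 = 0.337.
- All pairs of sleep variable and other measure: 8 × 15 = 120 screens, and 120 × 0.05 = 6 expected false hits. This holds in either direction and whatever the correlations.

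**Both steps, by simulation.** Assumptions: normal data, n = 48, every candidate pure noise, equal correlation between candidates, screen at p < 0.05. The entries are the share of final models holding at least one predictor at p < 0.05.

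| Candidates, removal threshold | corr. 0 | 0.3 | 0.5 | 0.7 |
|---|---|---|---|---|
| 15, removal 0.05 (1,500 runs) | 54% | 48% | 35% | – |
| 15, removal 0.10 (4,000 runs) | 52% | 45% | 36% | – |
| 8, removal 0.05 | – | 30% | 24% | 20% |

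With 15 candidates and removal at 0.10, the mean R-squared of models that kept anything was 0.13 to 0.15, where the true value is zero. A looser screen of 0.20 with removal at 0.10 gave 54% at correlation 0.3, against 45%.

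**Effect of sample size.** With n = 38 (an assumed loss of about 20%), 15 candidates and removal at 0.10, the shares were 54%, 45% and 37%, almost unchanged, while mean R-squared rose to 0.16–0.18. The false-positive rate comes from the number of candidates and the selection; the small sample mainly inflates apparent fit.

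**Group omitted.** If treatment shifts both variables by d within-group SDs in equal groups, the pooled correlation it induces is (d²/4) / (1 + d²/4). For d = 0.6 this is 0.09/1.09 = 0.08; for d = 1.0 it is 0.25/1.25 = 0.20. In simulation (15 candidates, correlation 0.3, removal 0.10, every variable shifted by d), the share of models with a predictor at p < 0.05 was:
- d = 0.6: 53% without group, 43% with group.
- d = 1.0: 82% without group, 45% with group.

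Adding group removes the treatment-induced part but leaves the selection problem where it was.

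**The case against.** The strongest reply is that this is a secondary analysis in a pilot, that Research Objectives calls it exploration, and that the article condenses a fuller document. That limits the weight of the point. It does not remove it, because the selection procedure is stated outright and not left open, and Data Analysis speaks of establishing relationships.

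The reply also rules out several stronger readings that a reader might infer:

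- *That group is left out of the model.* The article is silent. It does not say whether baseline, follow-up or change scores are modelled, and in a baseline model there is no treatment effect to mix in.
- *That 15 predictors will be screened.* This requires sleep to be the outcome. The end of the Background speaks of the impact of sleep changes on psychological and physical measures, which suggests the reverse and about 8 candidates.
- *That the models will be mostly noise.* The simulations assume no true association at all. The Background describes depression as strongly associated with disturbed sleep and links pain with sleep, so some selected predictors may well be real. The rates show how little a p-value below 0.05 proves here, not what share of findings would be false.
- *That a spurious model somewhere is practically certain.* The figure 1 − (1 − 0.35)^8 = 0.97 treats the eight sleep variables as independent, but seven come from one actigraphy recording. With outcomes correlated 0.7 and candidates correlated 0.3 to 0.5, one simulation gave 87–94% and a repeat 84–92%. The expected count of 6 false hits needs no independence assumption and is the safer figure.
- *That function and mood changes are not analysed.* Change scores and confidence intervals are planned for them; only a between-group comparison is not named.

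**Conclusion.** The point holds as a criticism of the stated selection procedure. Under a global null, a predictor at p < 0.05 survives in about 35–54% of final models with 15 candidates and about 20–30% with 8 correlated candidates, where a reader would take the rate to be 5%. Mean apparent R-squared with 15 candidates is about 0.13–0.15. These figures rest on the candidate count inferred from the instrument list, a 0.05 screen (the only threshold in the text), assumed removal thresholds of 0.05 or 0.10, and assumed equal correlations.

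The possible contribution of group is conditional on pooling post-baseline or change scores, modest at the protocol's own effect size of 0.6 and large only if the programme moves all measures strongly. The missing between-group comparison for function and mood is a small gap between objective and analysis. The harm is over-reading of the secondary models; the primary comparison is not affected.

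**What to change.** - Replace the univariate screen and backward elimination with a small prespecified model for the key sleep outcomes, for example sleep efficiency and PSQI. Name the dependent variable and say whether baseline, follow-up or change scores are used.
- Include group whenever post-baseline or change scores are modelled, along with the baseline value and a few predictors named before the data are seen. Which predictors, and how many within what 48 patients can support, is for the sponsor to choose.
- Report every coefficient with its 95% confidence interval, and describe the models as exploratory, so that Data Analysis matches Research Objectives.
- State that changes in function and mood will be compared between groups in the same way as the primary outcome.

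The cost is a change of analysis wording. The downside is that fewer predictors are explored and the choice has to be made in advance.
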